## Abstract

**Background::**

Knee injuries are a major injury concern for Australian Football players and participants of many other sports worldwide. There is increasing evidence from laboratory and biomechanically focused studies about the likely benefit of targeted exercise programmes to prevent knee injuries. However, there have been few international studies that have evaluated the effectiveness of such programmes in the real-world context of community sport that have combined epidemiological, behavioural and biomechanical approaches.

**Objective::**

To implement a fully piloted and tested exercise training intervention to reduce the number of football-related knee injuries. In so doing, to evaluate the intervention’s effectiveness in the real-world context of community football and to determine if the underlying neural and biomechanical training adaptations are associated with decreased risk of injury.

**Setting::**

Adult players from community-level Australian Football clubs in two Australian states over the 2007–08 playing seasons.

**Methods::**

A group-clustered randomised controlled trial with teams of players randomly allocated to either a coach-delivered targeted exercise programme or usual behaviour (control). Epidemiological component: field-based injury surveillance and monitoring of training/game exposures. Behavioural component: evaluation of player and coach attitudes, knowledge, behaviours and compliance, both before and after the intervention is implemented. Biomechanical component: biomechanical, game mobility and neuromuscular parameters assessed to determine the fundamental effect of training on these factors and injury risk.

**Outcome measures::**

The rate and severity of injury in the intervention group compared with the control group. Changes, if any, in behavioural components. Process evaluation: coach delivery factors and likely sustainability.

In 1994, the Commonwealth Government of Australia released its health strategy policy and national health goals and targets.^1^ The injury prevention/control strategy recognised sports injuries as a significant public health problem and a major barrier towards participation in sport/physical activity. Sports injury prevention has also been addressed in other Australian national public health frameworks for both physical activity promotion and sports safety.^2^ ^3^ For example, the 1997 *SportSafe Australia* framework^3^ recognised sports injuries as a potential adverse outcome of increased physical activity participation and emphasised their public health burden for both individuals and society with respect to the duration/nature of treatment, the amount of sport/working time lost, permanent damage/disability, reduced quality of life and other monetary costs.^3^ The most recent estimate of the annual cost of sports injuries to Australians is AUS$1.83 billion.^4^

Importantly, sports injuries are not an inevitable part of participation,^3^ and much can be done to prevent them and reduce their burden on Australian society.^2^ ^3^ ^5^ Despite this, a recent overview of the status of sports safety action in Australia concluded that the evidence base for the effectiveness of a full range of prevention measures is largely non-existent.^2^

## FOOTBALL INJURIES AS A PRIORITY PUBLIC HEALTH ISSUE

This project focuses on preventing knee injuries in Australian Football because it is one of the most popular team sports in Australia (with large numbers of both formal and informal community participants, including females). The Australian Bureau of Statistics has estimated that ∼2% of the general population and 3% of the male population participate in Australian Football.^6^ These figures rank Australian Football as the 13th most popular physical activity with respect to participation rates.

Unfortunately, Australian Football also has a high excess risk of injury. Epidemiological studies of medically treated sports injuries in Australia have consistently shown that Australian Football ranks as the sport associated with the highest number of presentations for injury treatment, accounting for more than 23% of all cases presenting to sports medicine clinics, emergency departments and general practice clinics.^7^^–^11 Moreover, Australian Football is ranked in the top 10 sports activities leading to injuries that are so severe they require admission to hospital (after an emergency department visit) in Australia.^8^ The prominence of Australian Football in the injury statistics remains even after participation rates are taken into account.^7^ ^11^

Australian Football is a contact sport and running game that involves periods of continuous physical activity, interspersed with periods of high-intensity activity, including unexpected, explosive and agile movements and heavy physical contact. These game features contribute to the high risk of injury. Although preventive measures have been adopted to varying degrees, the current lack of an evidence base limits the safety advice that can be given to players, their parents, coaches and sports administrators about the best injury prevention measures to adopt, while playing Australian Football.^2^

## PREVENTION OF KNEE INJURIES

From a public health point of view, Australian Football-related knee injuries are of particular concern because of their high frequency, associated treatment/rehabilitation costs, absence from participation and other long-term sequelae. Knee injuries account for >30% of all medically treated Australian Football injuries^9^ ^11^ ^12^ and are the most expensive to treat and rehabilitate, especially if they require reconstructive surgery. On the basis of the best available data, we estimate that, if 50% of Australian Football-related knee injuries could be prevented, the annual savings to the Australian community would be of the order of $60 million.

Knee injuries are defined as those to the ligaments surrounding the knee joint. This excludes injuries to the patella and surrounding muscles, eg, the hamstring, but does include tears or partial/full ruptures of the anterior cruciate ligament (ACL) and medial cruciate ligament, meniscal tears and other ligament strains. Ligament injuries are essentially a neuromuscular and biomechanics problem, in that ligaments fail when applied physical loads exceed tissue strength. The critical factor in lowering the incidence of knee joint ligament injury is thus reduction in tissue loading.^13^

Previous research has shown that manoeuvres common to Australian Football, such as running and side stepping, can place large external loads on the knee joint^14^ ^15^ and have the potential to cause injury.^16^ ^17^ Ligament loading has been found to depend on: (*a*) the external loads applied to the joint; (*b*) the joint posture when these loads are applied; and (*c*) the ability of muscles surrounding the joint to reduce ligament loads.^13^^–^18 Alterations in neuromuscular and biomechanical factors can reduce ligament loading and reduce the potential for non-contact ligament injury by: (*a*) reducing the external loads applied to the joint; (*b*) changing knee joint posture and motion to reduce load; (*c*) improving the muscles’ abilities to counter large loads; and/or (*d*) improving the ligaments’ ability to withstand large loads.

It has been proposed that the most appropriate intervention strategy to achieve these neuromuscular and biomechanical changes is a well-designed exercise programme.^19^^–^21 Prior research provides the rationale for training programmes (including skill-based, balance and perturbation) to reduce ACL loading and therefore risk of injury in Australian Football.^19^ These intervention strategies include plyometric, perturbation and skill training as well as traditional proprioceptive training. Specific technique factors involved in performing sporting actions to decrease ACL loading and risk of injury have been identified.^14^ ^15^ ^22^ These theories have been confirmed in a randomised controlled trial (RCT) of 50 elite footballers: an aggressive balance-training programme was shown to (*a*) increase the level of hamstrings and quadriceps co-contraction and (*b*) reduce frontal plane knee loading by 35%. Both of these adaptations would reduce knee ligament loading and theoretically lower injury risk.

Although preventing sports injuries has been defined by the Australian National Health and Medical Research Council (NHMRC) and others as a priority research area, the effectiveness of exercise training programme modalities to prevent knee injuries in Australian Football, and indeed in most other sports, have not previously been undertaken.^2^ ^5^ Although it is common for specific exercise programmes to be undertaken by high-level/elite Australian Football players, these are generally promoted as a means of performance enhancement and have not been widely adopted at the broad community level of play. Furthermore, some of the more traditional “off-field” training regimens for community sport may actually increase knee loading in Australian Football game movements.^22^ ^23^ There is a particular need for the development of exercise training programmes for community-level players, as they have a high risk of knee injury and the focus of their involvement is continued safe and healthy participation and not performance.^2^

## RATIONALE FOR COMPONENTS OF AN EFFECTIVE EXERCISE TRAINING PROGRAMME

As jumping and landing manoeuvres have been implicated in causing ACL injuries, plyometric training (which involves jumping, bounding and landing to improve performance in explosive manoeuvres) has the potential to lower the risk of injury. Indeed, both this training and increasing jumping and bounding performance have been used to reduce the incidence of knee injuries in young female athletes.^24^ There is also some evidence that traditional proprioceptive training can reduce the incidence of ACL injuries.^20^ This training places demands on both whole-body balance and joint stability and can alter the voluntary and reflexive muscle activation patterns that may be in effect during sporting actions and potentially reduce the loads placed on the ligaments of the knee.^18^ ^22^ ^25^ ^26^ Recent research has elucidated the neuromuscular adaptations that stem from proprioceptive training^18^ ^25^ ^27^ and how these changes decrease the risk of ACL injury through reducing the loading of knee ligaments.^14^

Another exercise modality, whole-body perturbation training, is beginning to receive attention for its effect on neuromuscular mechanisms that enhance joint stability and decrease ligament loading.^19^ ^21^ ^28^ For example, whole-body perturbations applied to ACL-deficient subjects have been shown to improve dynamic knee joint stability and function and to reduce clinical symptoms.^21^ Knee-specific perturbation training which stimulates ligament mechanoreceptors in the knee could enhance voluntary movement control to improve joint stability and reduce ligament loads and injury risk.^19^ ^21^ ^28^

Skill training involves providing players with a qualitative description of techniques that will minimise their risk of injury while performing specific sporting movements (eg, cutting and landing). Changing torso movement relative to foot placement, lowering body centre of mass, increasing knee flexion during ground contact and increasing hamstring/quadriceps co-contraction during pre-foot contact and early and mid stance are technique modifications that have been shown to reduce frontal plane knee loading^14^ ^15^ ^22^ and loading on the ACL.^17^ ^19^ ^29^ Cowling *et al*^30^ have shown that it is possible to learn to use increased knee flexion angle when landing using verbal feedback. Other work has also shown that performing sporting tasks in an unanticipated manner increases external knee loads and compromises activation patterns that stabilise the knee and reduce ligament loading.^18^ Skill training should therefore include drills that ensure players are familiar with making “unanticipated” or “spur of moment” side steps.

This paper describes the aims, study design and methodology of the Preventing Australian Football Injuries with eXercise (PAFIX) Study. This study was designed according to the CONSORT statement.^31^ It is being conducted over the 4-year period of 2006–2009. The study is funded by a nationally competitive research project grant from the (Australian) National Health and Medical Research Council.

## RESEARCH AIMS AND HYPOTHESES

The PAFIX project aims to:Reduce the number of Australian Football-related knee injuries using appropriate intervention strategiesEvaluate the effectiveness of exercise intervention strategies targeting neuromuscular and biomechanical variables for reducing injury ratesIn so doing, it proposes to formally evaluate the effectiveness of exercise training programmes (a widely promoted injury prevention measure) to prevent knee injuries in community-level footballers.

Specific hypotheses are:

The rate of knee ligament injuries will be reduced after a targeted exercise training interventionNeuromuscular and biomechanical variables measured preseason will be related to injury riskThe neural and biomechanical adaptations resulting from the exercise training intervention will be associated with decreased risk of injury

On the basis of previous laboratory studies undertaken by us and referenced elsewhere in this paper, it is further hypothesised that these injury reductions will be related to the following changes after the specific training programmes:

The kinematics during cutting and landing tasks will be different pre to post training in the intervention group, compared with controlsKnee joint loading will be reduced pre to post training in the intervention group, compared with controlsMobility in the intervention group will be improved after training, and compared with controlsThe co-contraction of knee muscles during cutting and landing actions will be increased pre to post training in the intervention group, compared with controlsNeuromuscular measures will improve in the intervention training group pre to post training, and compared with controlsThese neuromuscular and biomechanical changes are related to a reduced risk of knee injury

## THE INTERVENTION BEING TRIALLED

As mentioned above, the intervention being trialled has previously undergone extensive laboratory and other pilot testing. Teams of Australian Football players are randomly assigned to either a control or intervention arm. The training intervention is a combination of skill-based training and perturbation training.^27^ The interventions are based on prior work which has elaborated and reviewed the essential features of, and rationale for, training programmes.^19^ ^27^ For example, some of the intervention components were trialled by us in a small-scale RCT with sub-elite Australian Football players: machine weights, free weights, aggressive balance training and combined machine weights and balance training. Eighty male players were randomly assigned to each of the four training and single control (no training) groups. The neuromuscular biomechanical tests applied before and after training were those previously published^14^ ^15^ ^18^ ^32^ ^33^ and incorporated side-stepping tasks that cause ligament injury in sport. Only the aggressive balance training, a major component of the intervention being trailed in this study, produced changes to reduce ACL loading in side-stepping tasks. These included an 18% increase in knee range of motion in the weight-acceptance phase of stance, a 35% reduction in the varus–valgus loading on the knee, and a 15% increase in the level of co-contraction of the hamstrings and quadriceps muscles.^23^ ^34^ Theoretically, these changes could reduce load on the ACL, thereby translating to a reduction in ACL injury risk. However, the only way to test this hypothesis is to examine the intervention in a larger combined epidemiological and biomechanical study, as is being undertaken here.

### Trial study arms

#### Control arm: control group (normal training programme)

At the community-level of play, most footballers undertake regular training sessions to prepare for the weekend games (matches). These sessions focus on game technique for performance purposes and to enhance the level of game skill, fitness, strength and conditioning. Typically these training programmes do not focus on specific exercises to reduce the risk of injury. Such training programmes are being used by the teams assigned to the control group. Control teams are not provided with any information about how to enhance these training programmes for injury prevention gains. A “sham” intervention has been given to the control teams in arm 1, and this is derived from what has been common practice for the teams plus a few extra exercises that are biomechanically distinct from those included in the intervention arm.

#### Intervention arm: normal training programme + intervention training programme

In addition to their usual training regimens, intervention teams are receiving a combination of skill and perturbation-type exercise training. This programme incorporates two general training modalities: (*a*) perturbation balance training and (*b*) training of technique to perform side-stepping, crossover and landing actions.^15^ ^25^ ^27^ In balance and perturbation training, the task difficulty progresses from standard proprioceptive training to performing sporting actions (eg, kicking, hand-balling) while being perturbed by the trainer. The purpose of perturbing a player is to stimulate the knee ligament mechanoreceptors, enhance voluntary movement control leading to improved joint stability, reduce ligament loads and reduce the risk of injury.^15^ ^19^ ^28^ The perturbation-training programme involves a circuit arrangement to minimise the amount of equipment required. Each circuit station includes a different item of equipment such as a mini-trampoline, aerobic steps, tilt boards, round and square wobble boards, roller boards, Dura discs and Swiss balls. There are different exercises to perform at each station, with the exercises becoming progressively harder as the player becomes more competent. Typical progressions at each station include: performing the exercises with eyes open to eyes shut; doing exercises with no external force being applied; catching and passing a ball; performing exercises while the board or person is being pushed. Most exercises progress from balancing on two feet, to balancing on one foot, to retaining balance while performing movements such as squats. All items of equipment used in the intervention training programmes are currently available from sports equipment suppliers and are relatively inexpensive (eg, wobble boards cost about AUS$40.00) and so are not prohibitive for uptake by community-based sports teams.

It is known that side-stepping techniques lower knee ligament loading and therefore the risk of injury.^14^ ^15^ ^22^ Individual player side-stepping techniques are videotaped and analysed using SiliconCoach software. This software has graphic tools that enable correct and incorrect techniques to be emphasised. Using processed video data, players are taken slowly through each action, identifying and practising the important factors of the technique that must be implemented to make the action safer. Techniques are first practised with the player knowing which actions are to be carried out to achieve the correct technique. Then actions are performed in situations where players do not know which direction or when the action is to be performed until just before execution when instructed by a trainer. As the player becomes more proficient, they progress from performing actions in isolation to performing actions against other players in a simulated match environment. All exercises and their progressions concentrate on working the muscles surrounding the knee joint, improving these muscle activation patterns to increase stability of the knee, and increasing knee flexion angle during task performance. A common method used in knee rehabilitation is self-palpation of the muscles, so that players are familiar with activating specific muscle and therefore learn how co-contraction of muscles “feels”, so that they can practise these actions in “real-life” sporting tasks just before heel strike. Obtaining increases in knee flexion angles during all tasks is facilitated by simple verbal instructions.^30^

## THE RCT METHODOLOGY

The study is a cluster-randomised RCT evaluation of the exercise training programmes in the field over two playing seasons. The cluster randomisation design is the optimal one for implementation in the field. Australian Football is the sport of choice because of its high public health priority ranking for sports injury prevention action and the fact that all of the proposed epidemiological, fieldwork and laboratory-based methodologies have all been fully trialled in this sport. Teams of Australian Football players from community-level Australian Football competitions will be invited to participate in the trial because they provide a natural grouping of players. Furthermore, injury interventions that are adopted into Australian Football practice will need to be implemented at the team level.

The field-based epidemiological methodology has already been pilot tested, adopted in other sports injury prevention RCTs and prospective cohort studies, and published in the international peer-review literature.^11^ ^12^ ^35^^–^43 Injury surveillance and detailed monitoring of exposure (ie, Australian Football participation) and compliance (with each intervention) are undertaken using the previously reported epidemiological methods.^11^ ^12^ ^35^ ^38^ ^41^^–^43 The study also includes a detailed evaluation of player attitudes, knowledge, behaviours and compliance, both before and after the intervention is implemented on the basis of similar studies.^44^^–^50

The proposed RCT is a multi-site study, being conducted in both Ballarat (Victoria, Australia) and Perth (Western Australia). It has purposely been designed as a multi-state trial because there will be fewer control and training teams in each state, leading to a reduced risk of contamination across study arms, ie, controls finding out about the training programmes for the training intervention groups. Although ground conditions appear to be related to injury risk in elite players, no study has yet explored this for community-level players. A further advantage of our two-state study design is that the different ground conditions in the states will enable an assessment of the possible crossover effect of training and ground conditions.

### Recruitment

With the assistance of the parent Australian Football bodies, we identified local Australian Football leagues and their contact details of all suitable clubs/teams. The teams were randomly ordered and then invited to participate in the study until the quota was reached, with the restriction that, overall, 50% of the teams were from Ballarat and 50% from Perth. In agreeing to participate in the study at this stage, no team was informed to which arm of the RCT they would be assigned. Once teams had expressed an interest in participating in the trial, an attempt was made to recruit all players from these teams; informed consent was obtained from them. All players are aged ⩾16 years. When team recruitment was complete, whole teams were randomised to the two study arms in each state. Study teams were recruited into the larger study, even if some players did not give their informed consent for us to monitor them. This recruitment methodology has previously been used in another sports injury prevention RCT and shown to lead to unbiased recruitment of teams and players.^37^ ^41^ ^51^

### Sample size

The intervention is being implemented during training sessions and its effects measured during games. A team consists of 18 members and a game lasts ∼100 min (four quarters of ∼20 min plus ∼5 min time added on). Over a 6-month playing season, each team has ∼20 games and so each team will contribute ∼600 game-hours of exposure to knee injury risk. We used a standard cluster randomised trial sample size calculation for comparing rates between a control arm and an intervention arm.^52^ The knee injury rate in the control arm was estimated as 20 per 1000 game-hours. This figure is based on the observation of 60.2 injuries (of all kinds) per 1000 game-hours (from data from Finch *et al*^11^) and an assumption that approximately one-third of Australian Football injuries involve the knee. To have 80% power to detect a reduction in the injury rate of 35% (ie a rate ratio of 0.65) in the intervention arm compared with controls, we would require 8.8 teams in each arm. This calculation does not take account of any clustering effects of injuries by team. From the same data,^11^ we estimate that the coefficient of variation of team injury rates will be 0.35 (ie, standard deviation of team injury rates divided by mean of team rates). Assuming that the clustering effect will be identical in the intervention arm, the number of teams required must be multiplied by 2.27, ie, 8.8×2.27 = 20 teams per study arm over the 2 years. Thus 20 teams (10 in Ballarat, 10 in Perth) will be randomly allocated to each arm of the study across the two playing seasons.

For continuous biomechanical outcome data measurements, we plan to sub-sample six players per team. Given 20 teams per study arm, this will give us 80% power to detect effects of size (*a*) 0.44 or (*b*) 0.63 standard deviations (SDs) between study arms assuming a clustering effect described by an intracluster correlation coefficient of (*a*) 0.1 or (*b*) 0.4. The SDs refer to total player-to-player variability in the biomechanical outcome, and the intracluster correlation coefficient is the ratio of between-team variability to total variability. To achieve six players with complete biomechanics data, we will enlist eight, expecting ∼20% dropout based on our previous training study. These sample size calculations also provide a conservative lower bound for power for the analysis of attitude scores, as they were based on six players per team, and the change in attitude scores will be available for closer to 18 players. The study will therefore have >80% power for detecting changes in neuromuscular, biomechanical and attitude parameters as described by an effect size of 0.44 SDs.

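### The claim of more than 80% power for changes of 0.44 SD states no pre-post correlation: for unadjusted changes in the six-player tests, power could be about 50% to 79.5% at correlations of 0 to 0.5, and the 20-team figure does not cover the Perth-only measures

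*Protocol article*

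**What the plan says.** All of the power statement is in the Sample size section of the protocol article.

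- Subsample: "For continuous biomechanical outcome data measurements, we plan to sub-sample six players per team".
- Result: "Given 20 teams per study arm, this will give us 80% power to detect effects of size" 0.44 SD when the ICC is 0.1, or 0.63 SD when it is 0.4.
- Scale: "The SDs refer to total player-to-player variability in the biomechanical outcome", and "the intracluster correlation coefficient is the ratio of between-team variability to total variability".
- Dropout: eight players per team are enlisted so that six have complete data.
- Attitude scores: the calculation is called a conservative lower bound, because change scores will be available for nearer 18 players per team.
- Conclusion: "The study will therefore have >80% power for detecting changes in neuromuscular, biomechanical and attitude parameters as described by an effect size of 0.44 SDs".

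Three other sections bear on this. Research aims and hypotheses frames the kinematic, knee-loading, mobility, co-contraction and neuromuscular hypotheses as pre-to-post or after-training comparisons with controls. The section on biomechanical, neuromuscular and mobility outcome measures schedules two tests, preseason and mid-season. It places the full laboratory battery in Perth only, with four field tests repeated in Ballarat: knee movement and position sense, isometric strength, standing balance and the agility cone test. The Analysis section names generalised estimating equations (GEE) for the biomechanical outcomes. It does not say whether the response is the change, the mid-season value or the mid-season value adjusted for preseason. For attitude scores it does say that changes are compared across arms.

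**The concern.** The calculation is scaled to the spread of an outcome between players, and its conclusion is about changes. The two are linked by the pre-post correlation r: with equal variances at both tests, the SD of a change is the single-test SD times √(2(1 − r)). At r = 0.5 the factor is 1 and the figures carry over. Below 0.5 the change is more variable than a single test. There is no slack to absorb this, since power at 0.44 SD is 79.5% before any inflation.

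This is the only power statement for the mechanism hypotheses, which the article presents as a main strength of the project. If it is too optimistic, a null result on these measures could be given more weight than it deserves. The statement also rests on 20 teams per arm, which the measures taken only in Perth do not have.

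**Working it through.** **Inputs from the protocol article.** Teams per arm c = 20, of which 10 are in Perth; players per team m = 6, or about 18 for attitude scores; ICC = 0.1, the case carried into the concluding sentence; effect 0.44 SD.

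**Assumptions.** Two-sided α of 0.05 with a normal approximation (not stated, but it reproduces the printed figures); r from 0 to 0.7 (no value is given); an ICC of 0.1 for the change and for the baseline-adjusted value; the SD is that of one test.

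**Formulas.** Effective players per arm n = cm / (1 + (m − 1)·ICC). SE = f·√(2/n). Detectable difference at 80% power = (1.960 + 0.842)·SE. Power = Φ(0.44/SE − 1.960). The factor f is 1 for one test, √(2(1 − r)) for an unadjusted change and √(1 − r²) for a baseline-adjusted value.

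**1. The plan's own figures.**
- ICC 0.1: n = 120/1.5 = 80, SE = √(2/80) = 0.158, detectable difference 0.443 SD. Power at 0.44 SD is 79.5%.
- ICC 0.4: n = 120/3 = 40, SE = 0.224, detectable difference 0.626 SD. Power at 0.63 SD is 80.4%.

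Both reproduce with f = 1 and no r.

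**2. Changes and baseline-adjusted values, effect 0.44 single-test SD.**

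| r | Unadjusted change, 6 players | Detectable change, 6 players | Baseline-adjusted, 6 players | Unadjusted change, 18 players (attitude) |
|---|---|---|---|---|
| 0 | 50% | 0.63 SD | 79.5% | 72% |
| 0.2 | 60% | 0.56 SD | 81% | 81% |
| 0.3 | 65% | 0.52 SD | 83% | 86% |
| 0.4 | 72% | 0.49 SD | 86% | 91% |
| 0.5 | 79.5% | 0.44 SD | 89.5% | 95% |
| 0.7 | 95% | 0.34 SD | 97% | over 99% |

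Worked line for r = 0.3, six players, unadjusted: f = √1.4 = 1.183; SE = 1.183 × 0.158 = 0.187; 0.44/0.187 − 1.960 = 0.39; Φ(0.39) ≈ 65%. For attitude scores, n = 360/2.7 = 133.

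**3. Sensitivity to the ICC of the change (r = 0.3, six players, unadjusted).** Power is 82% at ICC 0, 73% at 0.05, 65% at 0.1 and 53% at 0.2. A t reference with 38 degrees of freedom lowers power by about two points (63% at r = 0.3, 77% at r = 0.5).

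**4. Measures taken only in Perth.** With 10 teams per arm, n = 60/1.5 = 40 and SE = √(2/40) = 0.224. The detectable difference on a single test is 0.626 SD, and power at 0.44 SD is Φ(0.44/0.224 − 1.960) ≈ 50%. With baseline adjustment, power is about 54% at r = 0.3 and 79% at r = 0.7.

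**The case against.** A reader might infer that the printed power is an arithmetic error, or that it holds only if the two tests correlate at 0.5 or more. The document supports neither, for these reasons.

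- **The SD is not labelled.** The text does not say whether the outcome is one test or the change. If 0.44 SD means SDs of the change itself, with ICC 0.1 for that change, the stated power at 20 teams per arm stands at any r. This possibility remains open. The single-test reading is the more natural one, because the article lists the measures themselves as outcomes and names a change explicitly when it turns to attitude scores. Even so, a reader cannot tell which effect the 0.44 represents.
- **An unadjusted change score is not specified for the biomechanical outcomes.** The choice of response within the GEE is commonly left to an analysis plan, so its absence is not a fault. Baseline adjustment compares the same arms without the loss, so a correlation of 0.5 is not a general threshold.
- **The ICC of the change is assumed.** Stable team differences cancel in a change, so it may be below 0.1; it could also be above. The 65% at r = 0.3 is one value within a range of 53% to 82%.
- **Attitude scores are largely unaffected.** They are the one outcome explicitly compared as changes, and with about 18 players per team power stays above 80% from r of about 0.2. Only at lower correlations does the conservative-bound description fail (72% at r = 0).
- **The 20-team figures cannot describe the Perth-only measures.** This is correct and limits the point: a correlation of 0.5 would not rescue the claim for those measures, and baseline adjustment alone need not either.

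What survives is that the article itself moves from the spread of an outcome to power for changes, without the quantity that links them.

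**Conclusion.** The point holds in a conditional form. The printed detectable differences are arithmetically right, but the closing claim about changes does not follow from them without a pre-post correlation, and none is given.

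If the SD is that of one test and unadjusted changes are compared with an ICC of 0.1, power at 0.44 SD for the six-player tests done at both sites is about 50% to 79.5% for correlations of 0 to 0.5. It rises above 80% for higher correlations. The document gives no evidence on which part of the range applies. The laboratory measures confined to Perth are a separate case: with 10 teams per arm, power at 0.44 SD is about 50% even for a single-test comparison.

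This is worth correcting because the remedy is free. It does not show that the mechanism component is underpowered in every analysis the protocol allows.

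**What to change.** 1. In the GEE for each biomechanical and neuromuscular outcome, analyse the mid-season value with the preseason value of the same test as a covariate.
2. Reword the closing power sentence in Sample size as power for that baseline-adjusted difference between arms, in single-test SDs: at 0.44 SD and ICC 0.1, 79.5% at r = 0, 83% at r = 0.3 and about 90% at r = 0.5. The unadjusted figure is then a floor for non-negative correlations, provided the adjusted values have an ICC no larger than 0.1.
3. Limit the 20-teams-per-arm figure to tests done at both sites. For the Perth-only measures, state a detectable effect of about 0.63 SD unadjusted at ICC 0.1.
4. If change scores are kept, state the assumed correlation and the ICC of the change, and restate the detectable effect (for example 0.52 SD at r = 0.3 and ICC 0.1, both sites).

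The cost is one covariate that is already collected before training and a few reworded sentences, with no extra players or tests. The rewording does not add power to the Perth-only measures; it states what they can detect.
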